# Preoperative sequential short-course radiation therapy and FOLFOX chemotherapy versus long-course chemoradiotherapy for locally advanced rectal cancer: a multicenter, randomized controlled trial (SOLAR trial)

**DOI:** 10.1186/s12885-023-11363-7

**Published:** 2023-11-03

**Keywords:** Rectal neoplasm, Neoadjuvant radiotherapy, Short-course radiation, Consolidation chemotherapy, Disease-free survival, Randomized controlled phase II trial, Protocol

## Abstract

**Background:**

Preoperative (chemo)radiotherapy has been widely used as an effective treatment for locally advanced rectal cancer (LARC), leading to a significant reduction in pelvic recurrence rates. Because early administration of intensive chemotherapy for LARC has more advantages than adjuvant chemotherapy, total neoadjuvant therapy (TNT) has been introduced and evaluated to determine whether it can improve tumor response or treatment outcomes. This study aims to investigate whether short-course radiotherapy (SCRT) followed by intensive chemotherapy improves oncologic outcomes compared with traditional preoperative long-course chemoradiotherapy (CRT).

**Methods:**

A multicenter randomized phase II trial involving 364 patients with LARC (cT3–4, cN+, or presence of extramural vascular invasion) will be conducted. Patients will be randomly assigned to the experimental or control arm at a ratio of 1:1. Participants in the experimental arm will receive SCRT (25 Gy in 5 fractions, daily) followed by four cycles of FOLFOX (oxaliplatin, 5-fluorouracil, and folinic acid) as a neoadjuvant treatment, and those in the control arm will receive conventional radiotherapy (45–50.4 Gy in 25–28 fractions, 5 times a week) concurrently with capecitabine or 5-fluorouracil. As a mandatory surgical procedure, total mesorectal excision will be performed 2–5 weeks from the last cycle of chemotherapy in the experimental arm and 6–8 weeks after the last day of radiotherapy in the control arm. The primary endpoint is 3-year disease-free survival, and the secondary endpoints are tumor response, overall survival, toxicities, quality of life, and cost-effectiveness.

**Discussion:**

This is the first Korean randomized controlled study comparing SCRT-based TNT with traditional preoperative LC-CRT for LARC. The involvement of experienced colorectal surgeons ensures high-quality surgical resection. SCRT followed by FOLFOX chemotherapy is expected to improve disease-free survival compared with CRT, with potential advantages in tumor response, quality of life, and cost-effectiveness.

**Trial registration:**

This trial is registered at Clinical Research Information under the identifier Service KCT0004874 on April 02, 2020, and at Clinicaltrial.gov under the identifier NCT05673772 on January 06, 2023.

**Supplementary Information:**

The online version contains supplementary material available at 10.1186/s12885-023-11363-7.

## Background

Preoperative chemoradiotherapy (CRT) has long been the established treatment for locally advanced rectal cancer (LARC), effectively reducing the risk of local recurrence [1, 2]. However, despite the benefits, approximately one-third of patients with LARC experience relapse following preoperative CRT and surgery, with distant metastasis being the most common pattern of failure [2–6]. Recently, promising results of total neoadjuvant therapy (TNT) have been achieved in two trials: reduced disease-related treatment failure in the RAPIDO trial [4, 6] and increased disease-free survival (DFS) in the PRODIGE 23 trial [6]. As a results, TNT has emerged as the recommended treatment for LARC, emphasizing the need for timely and effective systemic therapy to eradicate micrometastases [7].

The main distinction between TNT and traditional preoperative CRT lies in the use of intensive chemotherapy before surgery. The RAPIDO and PRODIGE 23 trials differ in terms of tumor location, cT stage, cN stage, and circumferential resection margin status. Moreover, the TNT protocols vary in the sequence of treatments, types and cycles of neoadjuvant chemotherapy, and types of radiotherapy employed [4–6]. Currently, ongoing trials are evaluating different neoadjuvant treatment options for LARC.

While preoperative CRT has served as the standard treatment for LARC over the years and continues to be utilized in many countries, including South Korea [8, 9], short-course radiotherapy (SCRT) followed by delayed surgery has demonstrated comparable down-staging and surgical outcomes to CRT [10, 11]. Although systemic chemotherapy can be combined with both types of radiotherapy, a greater number of cycles of systemic chemotherapy can be scheduled with SCRT than CRT during the same treatment period.

Herein, we propose a neoadjuvant treatment protocol consisting of SCRT and four cycles of FOLFOX chemotherapy. Our randomized controlled trial aims to compare the 3-year DFS of patients with LARC treated with either preoperative CRT or SCRT followed by FOLFOX chemotherapy before total mesorectal excision (TME). We hypothesized that our protocol would yield superior systemic treatment effects compared to traditional CRT, reducing the total treatment period from the initiation of neoadjuvant treatment to the completion of adjuvant chemotherapy, and enhancing patient convenience.

## Methods

### Study setting

The present study is a parallel-group, multicenter, superiority, randomized, phase II trial. The participants will be enrolled in nine tertiary academic hospitals in South Korea. The trial flow scheme is presented in Fig. 1.

**Fig. 1 Fig1:**
[figure not shown]
Flowchart of the SOLAR trial. SCRT, short-course radiotherapy; FOLFOX, 5-fluorouracil with oxaliplatin; CRT, chemoradiotherapy; CT, computed tomography; MRI, magnetic resonance imaging; TME, total mesorectal excision

### Endpoints

The primary endpoint is the 3-year DFS, which is measured from the time of randomization until locoregional failure, metastasis, secondary cancer, or all-cause mortality. The data of patients who have not experienced any events by the time of the analysis will be censored at the last follow-up date. The Kaplan-Meier method will be used to calculate the survival rates. The secondary endpoints are the pathological complete response (pCR) rate; proportions of pathologic tumor regression grade (TRG) (Dworak [12], Mandard [13], AJCC TRG system [14]; R0 resection (microscopically clear resection) rate, 60-day postoperative surgical morbidity and mortality; treatment-related toxicity using the Common Terminology Criteria for Adverse Events version 5.0 (CTCAE v5.0); compliance with the study protocol defined as the completion of preoperative treatment, surgery, and adjuvant treatment; TRG based on magnetic resonance imaging (MRI) [15]); quality of TME [16]; 5-year DFS; 3/5-year overall survival (OS); loco-regional recurrence; distant metastasis; 3-year peripheral neuropathy grade (CTCAE v5.0); questionnaires of quality of life (QoL) using the Korean version of the European Organization for the Research and Treatment of Cancer Quality of Life Questionnaire Core 30 (EORTC QLQ-C30) version 3.0 [17]; QLQ-CR29 [18]; Low Anterior Resection Syndrome (LARS) score [19]; 5-item version of the International Index of Erectile Function (IIEF-5) [20]; retrograde ejaculation from inclusion to 2 years after surgery; and cost-effectiveness (direct cost, indirect cost, and quality-adjusted life-year).

### Study population, screening, and randomization

Patients with LARC are eligible for enrollment in this trial. They will be identified by the investigators and referred to the institutional multidisciplinary team for eligibility verification. The primary investigator will take charge of the final enrollment based on the inclusion/exclusion criteria (Table 1). Eligible patients who are willing to participate receive details of the study. After providing written informed consent at each hospital, the participants will be randomly assigned to either Arm A (experimental arm: SCRT plus mFOLFOX6) or Arm B (control arm: CRT). Block randomization at a ratio of 1:1 will be performed and managed by the central clinical research coordinator.

**Table 1 Tab1:** Inclusion and exclusion criteria

Inclusion criteria	Exclusion criteria
1) A male/female adult aged between 20 and 75 years 2) Race: Asian 3) Eastern Cooperative Oncology Group performance status 0–2 4) Pathologically confirmed rectal cancer (rectal cancer located 10 cm or low from the anal verge in pelvis MRI) 5) Histologic type: adenocarcinoma, mucinous carcinoma, and signet ring cell carcinoma 6) Locally advanced rectal cancer with one or more of the following factors based on pelvis MRI: cTanyN1-2, cT3-4N0, or presence of extramural vascular invasion 7) MRI findings such as pelvic lymph node metastasis, anal sphincter invasion, and T4b are not included in the exclusion criteria, which cases will be enrolled by the researcher’s discretion 8) Patients with appropriate organ (bone marrow, kidney, liver) function 9) A person who understands the study and willing to provide informed consent	1) Colon cancer or rectal cancer located more than 10 cm from the anal verge 2) Stage I rectal cancer (clinical stage cT1-2N0) 3) Clinically or pathologically diagnosed distant metastasis (cTanyNanyM1) 4) Familial adenomatous polyposis 5) Hereditary nonpolyposis colorectal cancer 6) History of chemotherapy or radiotherapy within 6 months 7) History of colorectal cancer or other malignant tumors within 5 years 8) Currently under treatment of malignant tumors (except for cured nonmelanoma skin or in situ cervical cancer) 9) Comorbidities that make it difficult to undergo chemotherapy or radiotherapy 10) Bone marrow suppression with neutrophil count < 2 × 10^9^/L or platelet count < 100 × 10^9^/L prior to the first chemotherapy 11) Peripheral sensory neuropathy with functional impairment (grade 2 or higher) 12) Severe renal function impairment (creatinine cleaning rate 30 ml/min or less) 13) Severe hepatic dysfunction 14) Genetic problems such as galactose intolerance, Lapp lactase deficiency, or glucose-galactose malabsorption 15) Taking tegafur, gimeracil, oteracil complex and those within 7 days of discontinuation 16) Taking sorivudine, brivudin 17) Significant heart disease or myocardial infarction within the last 6 months 18) Hereditary diseases or history of coagulopathy 19) Central nervous system disorders with disability or mental disorders 20) Pregnant or lactating women 21) Currently participating in other clinical trials or receiving research medication 22) Unhealed wounds, fractures, peptic ulcers, abscesses in the abdominal cavity 23) Active gastrointestinal bleeding 24) Active infection requiring injection with antibiotics 25) Emergency surgery 26) History of hypersensitivity to drug in the study protocol 27) Dihydropyrimidine dehydrogenase deficiency 28) Not willing to participate

MRI, magnetic resonance imaging

### Preoperative treatment

The participants in Arm A will receive SCRT (25 Gy in 5 fractions on consecutive days) followed by four cycles of mFOLFOX6 at 2-week intervals. The mFOLFOX6 regimen is composed of leucosodium 400 mg/m^2^ (or levoleucovorin 200 mg/m^2^ or leucovorin 400 mg/m^2^) and oxaliplatin (85 mg/m^2^) administered IV for 2-h and 5-fluorouracil (5-FU) 400 mg/m^2^ bolus followed by continuous infusion of 5-FU 2400 mg/m^2^ for over 46 h. The participants assigned to Arm B will receive CRT: a total dose of 45–50.4 Gy in 25–28 fractions given 5 times a week concurrently with capecitabine at a dose of 825 mg/m^2^ (twice daily) or bolus 5-FU 400 mg/m^2^ with leucovorin 20 mg/m^2^ (or levoleucovorin 10 mg/m^2^) on 1–4 days of the first and fifth week of CRT. Radiotherapy will be administered using 3-dimensional conformal or intensity-modulated radiotherapy. Clinical target volume will be delineated according to the guideline of the Radiation Therapy Oncology Group [21]. Details of radiation treatment planning will be determined at the discretion of participating radiation oncologists. Treatment-related toxicity will be monitored throughout the preoperative phase and chemotherapy dose modification can be made according to the protocol and investigator’s decision.

### Surgery

The surgery timing from the start of radiotherapy is comparable between the two arms. After the completion of preoperative treatments, the tumor will be reevaluated with computed tomography (CT) scan and MRI within 4 weeks before the scheduled surgery. TME will be performed at 2–5 weeks from the last cycle of preoperative chemotherapy in Arm A and at 6–8 weeks (maximum resting period of 10 weeks) after the last day of radiotherapy in Arm B. Surgical resection aims at achieving complete resection of primary tumor using TME with regional lymph node dissection. The type of surgical approach (open, laparoscopic, or robotic), starting point and direction of mesocolic and mesorectal detachment, location of major vascular ligation, splenic flexure mobilization, intestinal anastomosis, stoma creation, and surgical instruments will follow each investigator’s discretion. Postoperative complications will be recorded on the case report form for up to 60 days following surgery.

Surgical resection will be performed by a colorectal surgeon with sufficient knowledge and experience in rectal cancer surgery and treatment. All participating surgeons should have completed a fellowship in colorectal surgery and experience in more than 50 cases of rectal cancer surgery. The designated questionnaire presented in Supplementary Table 1 will be used for the recruitment of hospitals and surgeons. Each hospital has designated radiation oncologist(s), oncologist(s), pathologist(s), and radiologist(s) specializing in rectal cancer. The historical data on TME performed by the participating hospitals and surgeons is presented in Supplementary Fig. 1. The surgeons must submit unedited rectal cancer surgery videos to obtain approval from the research steering committee before the study participation. To ensure the quality of surgery and standardized surgical procedures, discussion on rectal cancer surgery and video presentation will be performed at the investigator meetings twice a year during the enrollment period.

### Postoperative chemotherapy

Adjuvant chemotherapy is recommended for all patients and initiated within 4 weeks following TME. The decision to use adjuvant chemotherapy and the timing of its initiation will be determined by the investigators in charge of chemotherapy based on each patient’s postoperative condition. The duration of adjuvant chemotherapy is about 4 months, resulting in a total chemotherapy period of 6 months. Both arms will receive adjuvant chemotherapy according to the pathological stage as follows: capecitabine or 5-FU with leucovorin (or leucosodium or levoleucovorin) for ypStages 0 to I and mFOLFOX 6 for ypStages II to III. In case of Stage IV confirmed before or at the time of surgery, additional treatment is determined by the institutional multidisciplinary team.

### Pathological evaluation

Pathological evaluation will be performed by the dedicated pathologists specializing in rectal cancer at each institution according to the AJCC Cancer Staging manual, 8th edition [14], and recorded using the pathological report form of the study, which includes the number of harvested/metastatic lymph nodes, length of proximal/distal/circumferential resection margin, and TRG using at least one of the three TRG systems (AJCC [14], Dworak [12], and Mandard [13] TRG system). The quality of the resected specimen will be classified for mesorectum and sphincter complex in case of abdominoperineal resection [22].

### Follow-up

Each participant will undergo regular follow-up until 5 years following surgery for history and morbidity/toxicity assessment, physical examination, measurement of carcinoembryonic antigen (CEA), and assessment of questionnaires of QoL. Toxicity will be evaluated and recorded according to CTCAE v5.0. Furthermore, CEA will be measured at 3 months following surgery and every 6 months thereafter. Abdominopelvic and chest CT scans will be performed every 6 months during the first 2 years and then annually during the following 3 years. QoL assessment using EORTC questionnaires QLQ-C30 and QLQ-CR29, LARS score for all patients, and IIEF-5 for male patients will be performed at 3, 6, 12, and 24 months.

### Translational research

Translational research using tumor tissue and blood will be conducted to interpret the clinical outcomes, treatment response, and prognosis in association with the molecular biological characteristics of rectal cancer. A specified protocol for the collection and preparation of fresh tissue and blood at different treatment stages will be given to all participating hospitals. Participation in the translational components of this trial is optional and subject to regional capacities. Samples will be collected and used after obtaining participant consent.

### Sample size calculation

The 3-year DFS following preoperative CRT is expected to be 70% based on literature [23–27]. We hypothesized that the experimental arm would have a 10% improvement in 3-year DFS compared with the control group. This corresponds to a hazard ratio of 0.626 between the two arms (experimental /control). Assuming an 80% statistical power, a one-sided alpha level of 0.05, a minimal accrual duration of 36 months, and a minimal follow-up of 36 months, a total of 113 events will be needed to observe the expected difference using the one-sided log-rank test. Assuming a 5% rate of patients who are not informative or lost to follow-up, a total of 364 patients will be enrolled in this study, with 182 patients in each group.

### Statistical analysis

The primary endpoint will be analyzed according to the intention-to-treat principle in patients who are randomized and receive preoperative treatments. Secondary analyses will be conducted using the per-protocol principle, considering only patients with sufficient compliance with the protocol. The Kaplan–Meier curve will be used to analyze the survival outcomes and the log-rank test for the prognostic factors. The chi-squared test will be employed to compare categorical data between the two groups and Student’s *t*-test for continuous variables. The effect of covariates on the endpoints will be evaluated using the Cox proportional-hazards model. QoL, assessed using questionnaires, will be expressed as mean, standard deviation, median, minimum, and maximum values. A mixed model for repeated-measure analysis with the assumption of an unconstructed covariance structure will be applied for QoL comparison. Least-square mean estimates will be calculated for *post hoc* analyses to compare the two treatment groups at each time point and evaluate any changes from the baseline scores. All tests will be two-sided, and *P*-value < 0.05 will be considered to indicate statistically significant differences. This trial has no plan for interim analysis. Missing data for the primary endpoint will be censored at either the last assessment date or the trial deadline, whichever is earlier. Because the primary endpoint is presented as recurrence or not, there are no outlier data. If there are missing values for the secondary endpoints, the last observation carried forward method will be employed to impute for the missing data with the most recently available data, and the Grubb and Cochran tests will be adopted to determine outliers if suspected.

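### The primary DFS set is called intention-to-treat but admits only randomized patients who receive preoperative treatment, and no all-randomized analysis is named.

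*Protocol article*

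**What the plan says.** The Statistical analysis section defines the primary set in one sentence: "The primary endpoint will be analyzed according to the intention-to-treat principle in patients who are randomized and receive preoperative treatments". The next sentence gives the only other set: "Secondary analyses will be conducted using the per-protocol principle, considering only patients with sufficient compliance with the protocol".

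Under Endpoints, DFS is "measured from the time of randomization until locoregional failure, metastasis, secondary cancer, or all-cause mortality". Under Study population, screening, and randomization, the order of steps is fixed: "After providing written informed consent at each hospital, the participants will be randomly assigned to either Arm A" (or to Arm B). Treatment comes after that.

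The Preoperative treatment section gives Arm A "SCRT (25 Gy in 5 fractions on consecutive days) followed by four cycles of mFOLFOX6 at 2-week intervals" and Arm B "a total dose of 45–50.4 Gy in 25–28 fractions given 5 times a week concurrently with capecitabine" or bolus 5-FU. No masking is described.

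**The concern.** An intention-to-treat set is fixed at randomization. This one is fixed later, by whether the patient went on to receive preoperative treatment. A patient who is randomized and then refuses, withdraws, is found to have metastasis, or dies before treatment leaves the primary analysis. Metastasis or death in that interval is a primary event under the Endpoints section, yet the Statistical analysis section removes the patient who had it.

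The arms differ visibly: 5 fractions and four intravenous cycles against 25–28 fractions with capecitabine or 5-FU. Patients and clinicians will know the allocation, so losses between allocation and treatment can depend on the arm. If they also relate to prognosis, the two treated groups are no longer comparable by design and the nominal error rate of the primary test is no longer guaranteed. The per-protocol set is narrower still, so nothing named in the article would show whether the exclusions mattered.

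**Working it through.** **The plan's own figure.** HR = ln(0.80)/ln(0.70) = 0.626, as stated. Schoenfeld events, 1:1, one-sided 0.05, 80% power: 4 × (1.645 + 0.842)² / (ln 0.626)² = 112.7, rounded up to 113, as stated. No design figure is in error; the issue is who enters the analysis.

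**Inputs for the illustration.**
- From the Sample size calculation section: control 3-year DFS 70%, 113 events, one-sided 0.05.
- From the Statistical analysis section: two-sided tests at 0.05.
- Assumed, because the documents give no figures: the share f of an arm that is excluded, and the 3-year event risk p of those patients. True DFS is set to 70% in both arms, so any apparent effect is bias. For scale, 5% of 182 is about 9 patients.

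**Formulas.**
1. DFS in the retained patients of an arm: S = (0.70 − f(1 − p)) / (1 − f).
2. Apparent HR (A/B): ln(S_A) / ln(S_B).
3. Shift of the test statistic: d = −ln(HR) × √113 / 2.
4. One-sided type I error: 1 − Φ(1.645 − d).
5. Two-sided: 1 − Φ(1.960 − d) falsely favours Arm A; Φ(−1.960 − d) falsely favours Arm B.

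**Worked case, 5% of Arm A only, p = 50%.** S_A = (0.70 − 0.05 × 0.50) / 0.95 = 0.7105. HR = ln(0.7105)/ln(0.70) = 0.958. d = 0.227. One-sided error = 1 − Φ(1.418) = 7.8%. Two-sided: 4.2% favouring Arm A plus 1.4% favouring Arm B, 5.6% in total.

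**Range of one-sided results (nominal 5.0%).**

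| Assumed exclusions | Apparent HR | Type I error |
|---|---|---|
| 2% of Arm A only, p = 50% | 0.984 | 6.0% |
| 3% of Arm A only, p = 50% | 0.975 | 6.5% |
| 5% of Arm A only, p = 50% | 0.958 | 7.8% |
| 5% of Arm A only, p = 60% | 0.937 | 9.7% |
| 5% of Arm A only, p = 30% (average risk) | 1.000 | 5.0% |
| 5% of Arm A only, p = 10% | 1.042 | 3.1% |
| 5% of Arm B only, p = 50% | 1.044 | 3.1% |
| 5% of Arm B only, p = 60% | 1.067 | 2.3% |
| 5% of each arm, p = 50% | 1.000 | 5.0% |

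The direction depends on which arm loses patients and on their prognosis. Exclusions matter only if they differ between arms and relate to outcome.

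**The case against.** The strongest reply is that very few patients may go untreated, that losses may be balanced, and that the bias could as easily work against the experimental arm. That stands: the table shows it, and it limits the claim to a comparison that can be biased, not one that is. It does not rescue the wording, because the label and the entry condition still contradict each other.

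Three stronger readings are tempting, and the documents do not support them.

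- **Patients who switch arms are dropped.** The sentence asks for receipt of preoperative treatment; it does not say the assigned treatment. A patient who switches still receives preoperative treatment and stays in the set, to be analysed as randomized.
- **The rule is uneven, because an Arm A patient who stops between radiotherapy and FOLFOX is excluded with no counterpart in Arm B.** This needs the plural to mean every component. The Conclusions section uses the plural for the two regimens, and completion belongs to the compliance endpoint and the per-protocol set. The natural reading is that treatment was started, which applies equally to both arms. The wording is loose, but the asymmetry is not shown.
- **Type I error rises to 7.8–9.7%.** Those values need poor-prognosis losses confined to Arm A and the one-sided test. Under the two-sided rule in the Statistical analysis section, the same two cases total 5.6% and 6.4%. The article leaves the choice of sidedness unresolved.

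It may also be said that a statistical analysis plan could define the set differently. It would then contradict this published sentence, which states a rule and does not merely omit one.

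**Conclusion.** The concern holds as a definitional error in the primary analysis set. The article states a post-randomization exclusion under an intention-to-treat label, starts the DFS clock before that exclusion operates, and names no all-randomized analysis. This holds on the mildest reading, under which any preoperative treatment qualifies.

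The consequence is less certain than the error. Its size and direction are unknown, because no exclusion rate or prognosis is given. With 5% excluded from one arm, the assumed cases run from 2.3% to 9.7% against a nominal one-sided 5.0%; balanced or average-risk exclusions leave 5.0%. The route by which losses differ between arms rests on inferring from the regimens that allocation is known. A reader should not conclude that the trial favours the experimental arm or that its error rate is already lost.

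**What to change.** Define the primary set as all randomized patients, analysed in the arm assigned whatever treatment they received. Continue outcome follow-up of patients who receive no preoperative treatment. Keep the patients who were randomized and started preoperative treatment as a named sensitivity analysis, with started defined identically for both arms.

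The 113 events and 364 patients need not change. The costs are small:
- **Follow-up.** Outcomes must be collected in a few untreated patients. The Follow-up section dates its schedule from surgery, so these patients need one dated from randomization.
- **Dilution.** Untreated patients may slightly weaken the observed effect. The sample size allowance ("Assuming a 5% rate of patients who are not informative or lost to follow-up") is not designed to cover this. As an assumed illustration, if 5% of Arm A had control-level DFS, Arm A would be at 0.95 × 0.80 + 0.05 × 0.70 = 0.795, the HR would be ln(0.795)/ln(0.70) = 0.643, and about 127 events would be needed for 80% power, not 113.

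The Current status section reports 182 of 364 patients recruited by July 2023, and no interim analysis is planned. On that published timeline the wording could be corrected before any efficacy comparison.

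### The per-protocol rule for secondary analyses makes no exception for compliance or safety; if it covers the secondary endpoints, the compliance endpoint is close to circular and others may be biased

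*Protocol article*

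**What the plan says.** In the Protocol article, Statistical analysis, two consecutive sentences set the populations. The first reads "The primary endpoint will be analyzed according to the intention-to-treat principle in patients who are randomized and receive preoperative treatments". The second reads "Secondary analyses will be conducted using the per-protocol principle, considering only patients with sufficient compliance with the protocol". No exception is made for safety or for compliance. The tests that follow name no further population; for categorical outcomes, for example, "The chi-squared test will be employed to compare categorical data between the two groups".

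The Endpoints section lists among the secondary endpoints "compliance with the study protocol defined as the completion of preoperative treatment, surgery, and adjuvant treatment" and "treatment-related toxicity using the Common Terminology Criteria for Adverse Events version 5.0". The same list contains 60-day postoperative morbidity and mortality, 5-year disease-free survival (DFS), 3- and 5-year overall survival, loco-regional recurrence and distant metastasis. DFS is counted from randomization.

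The article gives no threshold for the level of compliance that admits a patient to the per-protocol set.

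**The concern.** Set side by side, the two sentences most naturally map the primary endpoint to intention-to-treat and everything secondary to per-protocol. Several secondary endpoints cannot sensibly be estimated in a set chosen by compliance.

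- Compliance itself is the outcome, so selecting on it largely fixes the answer.
- Patients who stop because of toxicity are the ones a compliance filter can remove from the toxicity comparison.
- A patient who dies after surgery cannot complete adjuvant treatment, so 60-day mortality and overall survival can lose early deaths.
- A patient found to have metastases before or at surgery leaves the standard adjuvant path (Postoperative chemotherapy) and may drop out of the metastasis and recurrence comparisons.

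The arms differ in preoperative chemotherapy: four cycles of mFOLFOX6 after short-course radiotherapy, against a fluoropyrimidine given with long-course radiotherapy. The selection therefore need not be the same in both arms. At stake are the safety, feasibility and survival comparisons that would accompany the DFS result.

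**Working it through.** **The plan's own figure.** The point disputes no design number, but the event count was checked. With a hazard ratio of ln(0.80)/ln(0.70) = 0.626, one-sided alpha 0.05 and 80% power, Schoenfeld's formula gives 4 × (1.645 + 0.842)² / (ln 0.626)² = 112.7, that is 113 events, as stated. This count concerns the primary comparison and does not depend on the population used for secondary endpoints.

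**Compliance.** Let c be the true completion rate in an arm and s the share of the arm admitted to the per-protocol set, with every completer admitted (s ≥ c). The completion rate seen in the set is c/s. It equals c only if nobody is excluded, and it reaches 100% when the set consists of completers. Assume true completion of 75% against 85%, with 182 patients per arm:

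- All randomized: a difference of 10 points.
- Completers only (0.75 × 182 = 136.5 and 0.85 × 182 = 154.7, so roughly 136 and 155 patients): 100% against 100%, difference 0.
- A looser threshold admitting 85% of each arm: 0.75/0.85 = 88% against 0.85/0.85 = 100%, difference 12 points.

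The level is pushed up in every case in which someone is excluded. Even the direction of the error in the difference depends on the unstated threshold.

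**Toxicity, one arm.** Assume 35% have grade 3 or higher toxicity, 20% are excluded as non-compliant, and 70% of those excluded had such toxicity. The rate in the set is (0.35 − 0.20 × 0.70)/(1 − 0.20) = 0.21/0.80 = 26.25%, about 9 points too low. If instead the excluded patients have the same 35% rate as everyone else, the result is (0.35 − 0.20 × 0.35)/0.80 = 35%, with no bias.

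**Toxicity, between arms.** With true rate t, completion c1 among patients with severe toxicity and c0 among the rest, the rate among completers is t·c1 / (t·c1 + (1 − t)·c0). All rates below are assumed, with c0 = 0.90.

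| True rates | c1 | Rates seen | Difference |
|---|---|---|---|
| 40% v 25% | 0.50 in both arms | 27% v 16% | 11 points (true 15) |
| 40% v 25% | 0.70 in both arms | 34% v 21% | 14 points (true 15) |
| 40% v 25% | 0.90 in both arms | 40% v 25% | 15 points (no bias) |
| 40% v 40% | 0.50 v 0.80 | 27% v 37% | 10 points (true 0) |

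The difference can be preserved, reduced or created, depending on how strongly toxicity drives non-completion and on whether it does so equally in the two arms.

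**Survival, recurrence and mortality.** The same logic applies, but the documents give no rates from which to compute a figure. The mechanism is exclusion of patients whose early event prevented them from meeting the compliance threshold.

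**The case against.** The sentence speaks of secondary analyses, not secondary endpoints. It directly follows the population for the primary endpoint, and a per-protocol analysis in support of an intention-to-treat analysis of the same endpoint is a common arrangement. Later in the same section, the missing-data rule names the secondary endpoints explicitly when it means them. On this narrower reading, the populations for the secondary endpoints are left to the full protocol or analysis plan, neither of which is shown, and their absence from an article is no fault. This stands as a real alternative. It does not remove the point, because the article states a rule whose more natural reading is harmful and a reader cannot tell which is meant.

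The threshold may also be looser than full completion. The article foresees dose changes during preoperative treatment ("chemotherapy dose modification can be made according to the protocol"), recommends adjuvant chemotherapy while leaving its use to the investigators, and refers stage IV disease to the multidisciplinary team. None of these courses need count as non-compliance. This also stands. A reader might infer that compliance would read 100% in both arms, or that the survival analyses carry about 8 months of guaranteed event-free time. That period is built from roughly 3 months to surgery, up to 1 month to the start of adjuvant treatment, and about 4 months of it. Both inferences require the per-protocol set to be patients who finished everything, which the article does not say.

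Finally, adverse events are to be graded and recorded in the electronic case report form, and the monitoring board reviews them as enrolment proceeds. The data therefore exist for any analysis set. That makes the correction cheap, but it does not fix the set used for the final comparison.

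**Conclusion.** The concern holds conditionally. If the per-protocol rule covers the secondary endpoints, the compliance endpoint is close to circular whatever rates are assumed. Toxicity, 60-day mortality, overall survival, recurrence and metastasis are then biased only to the extent that toxicity, early progression or death leads to non-compliance. The treatment course described in the article makes such a link likely but does not establish it.

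A reader might go further and conclude that all secondary results are biased by construction, or that safety and survival would necessarily look too good and by different amounts in the two arms. The documents do not support that. Bias by construction is strictly true for compliance alone, and without a threshold neither the size nor the between-arm direction can be derived. The 26% against 35%, and every other rate above except the design inputs, are illustrations under assumption.

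This is more than a missing detail, because it concerns a rule that is written down. It should be corrected, but it does not touch the primary analysis or the sample size.

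**What to change.** Reword the sentence and name the sets:

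- Per-protocol: a supportive sensitivity analysis of DFS only, with the compliance threshold defined in advance.
- Compliance and the efficacy secondary endpoints: all randomized patients, by assigned arm.
- Toxicity: all patients who started study treatment.
- 60-day surgical morbidity and mortality: all operated patients.

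The stated primary set is limited to randomized patients who receive preoperative treatment. The new text should therefore say openly how the secondary efficacy set relates to it.

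The cost is wording and an additional analysis set, with no new data collection. The 113 events and 364 patients are unaffected. When the article was written, 182 patients had been recruited and no interim analysis was planned, so the clarification could be made before outcomes were compared.
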